### Data monitoring

#### Formal committee

An independent Data Safety Monitoring Board (DSMB) whose members have experience in clinical trials has been formed. Monitoring and reporting of adverse events will be conducted throughout the whole trial. If there are concerns about the quality of care, and or the safety of any interventions, the committee will have the authority to stop the trial subject to evaluation by the Institutional REB.

#### Study coordinating center and study committees

The Principal Investigator (PI) and the Study Coordinator (SC) will be based at Toronto Western Hospital, Toronto, Canada. This will be the coordinating center for the study. The Co-Investigators of this Study work at the various study sites. The PI and the SC will be responsible for preparation of the protocol and any revisions, preparation of study data collection forms (case report forms), and drafting the research consent forms.

The Steering Committee consists of the PI (AA), SC (DA), biostatistician (XC), and the senior investigator (AB). The Steering Committee will meet once every 6 months and its role will be to approve the main study protocol and any amendments, monitor and supervise the trial towards its overall objectives, review relevant information from other sources, and resolve any problems that arise at a system level. The Trial Management Committee consists of the PI (AA), SC (DA), two co-investigators (ZM, JK), and the senior investigator (AB). The role of this Committee will be to monitor all aspects of the conduct and progress of the trial, ensure that the protocol and the budget are adhered to, and take appropriate action to safeguard participants and the quality of the trial itself. The Data Monitoring Committee consists of clinicians and biostatisticians appointed by study sponsors who will provide independent assessment of the safety, scientific validity, and integrity of the study.

### Interim analysis

There will be no planned interim analysis unless any safety concerns arise during the conduct of the trial.

### Safety/harms

Continuous monitoring and documentation of any adverse events will be carried out throughout the trial. Any unexpected adverse effects will be recorded in the participant’s file and reported to the Institutional REB. Adverse events will be collected non-systematically (i.e., spontaneous reporting from open-ended questions during follow-ups) but these will be classified as non-serious (e.g., pruritus in the area of the RFN) and serious (e.g., neurological deficits) for the purpose of reporting of the study’s results.

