**Discussion:**

Neck pain secondary to cervical facet joint disease is prevalent and RFA of the CMBN is a validated treatment for relieving it. The conventional parallel technique can be technically challenging, and it can be associated with adverse effects while the newer end-on approach has the potential of being a simpler technique with less adverse effects. This trial will be the first non-inferiority study to compare the clinical efficacy of the end-on approach against the conventional parallel approach for RFN of CMBN in patients with chronic neck pain due to cervical facet joint disease.

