## Introduction

### Background and rationale

Parallel radiofrequency neurotomy (RFN) of the cervical medial branch nerves (CMBN) utilizing sharp straight needles was first demonstrated to be clinically efficacious in a randomized clinical trial (RCT) setting for the treatment of chronic neck pain following whiplash injury almost three decades ago [1]. Over the next 20 years, several other studies followed with variable success rates. In the early 2000s, in a consecutive series of cases, the authors reported a success rate (defined as the complete abolition of pain) of 46 and 26% following RFN of the CMBN at 6 and 12 months, respectively [2]. Previously, an observational study in the late 1990s had already reported a success rate (defined as abolition of pain) of 57 and 36% at the 6- and 12-month follow-up, respectively [3]. Later, in 2012, a study conducted in New Zealand reported a success rate (defined as greater than 80% pain relief) of 68 and 51% at 6 and 12 months post-procedurally, respectively [4]. In addition, the rate of complications between studies also showed variability throughout the years. The rates of temporary post-procedural dysesthesias have been noted to vary from 43 to 67%, while the rates of temporary cutaneous numbness have been reported to range between 36 and 58%. Of note, only the rates of post-procedural pain seem to be relatively concordant between authors, with reported rates varying between 95 and 100% among studies. This data was comprehensively analyzed in a systematic review published in the late 2010s by the Standards Division of the Spine Intervention Society (SIS), where the authors looked at the effectiveness and risks of fluoroscopically guided parallel (also called conventional) RFN of the CMBN [5].

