### Hypotheses

The primary hypotheses for this non-inferiority trial are that end-on lesioning for RFN of the CMBN is non-inferior to the parallel conventional technique for its impact on the intensity of pain relief and the proportion of patients with a positive analgesic response at 3 months after the intervention in patients with chronic, moderate-to-severe neck pain in the context of cervical zygapophyseal joint syndrome. The secondary hypotheses are that end-on lesioning for RFN of the CMBN is non-inferior to the parallel conventional technique for its impact function, quality of life, sleep, adverse effects of the interventions, analgesic intake at specified time points within 1 to 12 months after the interventions in patients with chronic, moderate-to-severe neck pain in the context of cervical zygapophyseal joint syndrome.

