The following are the *secondary outcomes*:Pain intensity: The between-group difference in mean NRS for pain intensity scores at 1, 6, and 12 months after the interventions.Incidence of analgesic response: The between-group difference in the proportion of patients with a positive analgesic response (defined as 50% or greater reduction in the NRS score for neck pain as compared to baseline) at 1, 6, and 12 months after the interventions.Neck pain-related disability: The between-group difference in the proportion of patients with a 10% or greater reduction in the Neck Disability Index (NDI) score at 1, 3, 6, and 12 months after the interventions.Participant-assessed improvement: The between-group difference in the proportion of participants reporting some or much improvement on the Patients’ Global Impression of Change (PGIC) scale at 1, 3, 6, and 12 months after the interventions.Quality of sleep and life: The between-group difference in the mean Pittsburgh Sleep Quality Index (PSQI) scores and EuroQol (EQ-5D-5L) scores at 1, 3, 6, and 12 months after the interventions. Sleep health will be assessed using PSQI, and actigraphy-measured variables respectively, including sleep duration, sleep quality, daytime sleepiness, sleep timing, and wakefulness after sleep onset.Procedure-related outcomes: The between-group difference in the duration of procedure, discomfort, radiation dose, and cost of the procedures.Actigraphy-collected physical activity and sleep: The between-group difference in the average physical activity and sleep duration as measured by wrist-worn actigraphy over 1 week prior to the procedure and 1 week prior to the 1-month follow-up after the interventions.Adverse effects of the interventions: The between-group difference in the incidence of peri-procedural complications and post-procedural adverse effects at 1, 3, 6, and 12 months after the interventions.Analgesic requirements: The between-group difference in opioid requirements as measured by daily oral morphine equivalents in milligrams averaged over the 1 week prior to the 1, 3, 6, and 12 months follow-ups after the interventions.The patient assumption of the group they were assigned to at 3-month follow-up after the study interventions

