### Sample size

The sample size was calculated using the Statistical Package for the Social Sciences (SPSS, IBM SPSS Statistics) software. A sample size of 72 participants (36 in each treatment group) will provide 80% power to detect a difference (inferiority margin), at 3 months after the intervention, in the mean NRS pain intensity scores (0–10 scale) between the two treatment groups being less than or equal to 1 point, given a standard deviation (SD) of 1.7 at the 0.05 significance level (alpha) using a two-sided two independent sample *t*-test. To satisfy both the non-inferiority and superiority hypothesis, we plan to recruit a total of 80 participants to account for a presumed 10% dropout rate. The sample size calculations and the assumptions underlying it are based on data published on RFN of nerves supplying other axial joints (lumbar facets, sacroiliac) for the relief of spinal pain [12, 13]. The chosen non-inferiority margin of less than or equal to 1 point (10%) is reasonable because a minimal clinically important difference in pain scores for a treatment to be considered efficacious is 2 points or 30% [14]. A non-inferiority study is justified to compare the end-on and parallel RFN lesions because similar efficacy is expected but there may be a lower incidence of adverse effects (e.g., patient discomfort) and better resource utilization (e.g., faster procedure time, lower radiation dose) with the end-on RFN technique.

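### Dysesthesia and numbness after discharge are sought only by open-ended questions, although their between-group incidence is a planned outcome; a short fixed checklist would make that comparison more dependable

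*Protocol article*

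**What the plan says.** Safety/harms in the protocol article fixes the method of collection: "Adverse events will be collected non-systematically (i.e., spontaneous reporting from open-ended questions during follow-ups". Events are then classed as serious or non-serious for reporting.

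Four other places depend on these data:

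- Outcomes (secondary): "The between-group difference in the incidence of peri-procedural complications and post-procedural adverse effects at 1, 3, 6, and 12 months after the interventions".
- Hypotheses: the secondary hypotheses state that end-on is "non-inferior to the parallel conventional technique for its impact function, quality of life, sleep, adverse effects of the interventions, analgesic intake".
- Sample size, justifying the non-inferiority design: "similar efficacy is expected but there may be a lower incidence of adverse effects (e.g., patient discomfort". Faster procedure time and lower radiation dose are given alongside.
- Abstract, Discussion: "the newer end-on approach has the potential of being a simpler technique with less adverse effects".

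Background and rationale names the effects to expect with the parallel technique. "The rates of temporary post-procedural dysesthesias have been noted to vary from 43 to 67" per cent, and temporary cutaneous numbness is put at 36 to 58%. Table 2 schedules adverse effects at 1, 3, 6 and 12 months and names no instrument for them.

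**The concern.** The sensory effects of interest are known in advance and are described as temporary. The first scheduled enquiry about adverse effects is at 1 month, and it is open-ended. A participant whose numbness or dysesthesia has faded by then, or who does not think it worth raising, is counted as event-free.

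Participants and outcome assessors are to be blinded, so any loss is probably similar in the two arms. Similar loss is still not harmless, because it shrinks the absolute difference between arms. Two conclusions are exposed:

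- A true reduction in sensory effects with end-on is harder to show.
- The secondary hypothesis that end-on is non-inferior on adverse effects is easier to support, because missing events pull the two arms together.

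No later analysis can recover events that were never asked about.

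**Working it through.** **The plan's own figure.** The article gives no rate, margin or power for adverse effects, so there is nothing to reproduce. The 36 per arm below is taken from Sample size as stated.

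**What is and is not affected**

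| Item | How recorded | Where |
|---|---|---|
| Procedural complications | By staff on the day | Post-procedural management; Intervention data |
| Discomfort | 0–10 | Table 2; Intervention data |
| Pain | NRS at baseline, straight after the procedure and at each visit | Table 2 |
| Opioid use | Daily morphine equivalents at each visit | Table 2; Post-procedural management |
| Dysesthesia, numbness after discharge | Open-ended question | Safety/harms |

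Only the last row lacks a systematic measure.

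**Effect of equal under-capture.** Let p1 and p2 be the true incidences (parallel, end-on) and s the share of events captured in both arms. The expected observed incidences are s·p1 and s·p2, so the observed difference is s·(p1 − p2). The risk ratio is unchanged, but it is estimated from fewer events. The distortion is therefore on the absolute scale, which is how I read the outcome as worded (a between-group difference in incidence).

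**Illustrative power.** The test is the uncorrected chi-square named in Statistical methods, two-sided 0.05, n = 36 per arm. With x and y events in the two arms and P = (x + y)/(2n), z = ((x − y)/n) / √(2P(1 − P)/n). Power is the sum of the two binomial probabilities, multiplied, over all (x, y) with |z| > 1.96.

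Inputs:

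- p1: the limits quoted in Background and rationale.
- Assumed: p2 = p1/2, and s = 0.5 in both arms.

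| Effect | True rates | Difference | Power, full capture | Observed at s = 0.5 | Difference | Power |
|---|---|---|---|---|---|---|
| Dysesthesia, low | 43% v 21.5% | 21.5 points | 52% | 21.5% v 10.75% | 10.75 | 24% |
| Dysesthesia, high | 67% v 33.5% | 33.5 points | 82% | 33.5% v 16.75% | 16.75 | 37% |
| Numbness, low | 36% v 18% | 18 points | 41% | 18% v 9% | 9 | 21% |
| Numbness, high | 58% v 29% | 29 points | 70% | 29% v 14.5% | 14.5 | 32% |

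The usual normal approximation agrees to within 2 percentage points in every cell.

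**Smaller assumed effects, full capture, same test:** 55% v 35% gives 39%, 55% v 40% gives 23%, and 43% v 30% gives 21%. In these cases the sample size limits the comparison before ascertainment does.

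**Non-inferiority direction.** Suppose end-on were truly worse, say 58% v 43% (assumed), a difference of 15 points. At s = 0.5 the observed rates are 29% v 21.5%, a difference of 7.5 points. Against any fixed absolute margin, the smaller figure looks more acceptable. The article states no margin for adverse effects, so only the direction can be given.

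**The case against.** The strongest reply is that most of the safety rationale is measured well. The Sample size section's one example of an adverse effect is discomfort, which is scored for every participant, as are procedure time and radiation dose. No passage predicts that end-on reduces dysesthesia or numbness in particular; those rates are background on the parallel technique. This stands. A reader might infer that all safety data rest on spontaneous report, or that the trial could not judge any of the advantages that justify its design. The documents support neither. What remains is the general expectation of fewer adverse effects, plus a stated outcome and hypothesis that cover the sensory effects.

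Second, open-ended questions at scheduled visits are a form of prompt. That is true, but they are not specific to any event, and the article itself calls the collection non-systematic.

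Third, the capture share and the end-on rates are assumptions, and with modest effects a checklist would not rescue the comparison. This also stands, and it is why the power figures are illustrations only.

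A reader might also infer that the trial's incidences could not be set beside the published rates. How those rates were ascertained is not in the documents, so that claim is not made here.

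Finally, a detail left to an unseen plan would be no finding. Here, however, the article states the method outright.

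**Conclusion.** The point holds for adverse effects after discharge, chiefly dysesthesia and cutaneous numbness. They are collected by an admittedly non-systematic method although their between-group incidence is a secondary outcome and adverse effects are part of a secondary non-inferiority hypothesis. The primary outcomes are untouched.

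The direction is firm if capture is incomplete and about equal in the two arms: the absolute difference shrinks in proportion, which can hide a benefit of end-on and eases a non-inferiority conclusion on harms. The size cannot be derived from the documents. Halved rates and 50% capture are assumptions, and under them power roughly halves across the quoted ranges for both effects. It would be wrong to read this as showing that ascertainment is the main limit on the comparison, since with smaller effects 36 per arm gives low power even if every event is captured. This is an inexpensive improvement worth making, not a flaw that undermines the trial.

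**What to change.** Keep the open question for unexpected events. At each existing follow-up (1, 3, 6 and 12 months), have the blinded assessor add a short fixed checklist for dysesthesia and cutaneous numbness: presence, severity, and onset and duration since the last visit. It can be asked by video or phone where the 6- and 12-month visits are virtual. Use the checklist items for the between-group incidence of these two effects, and report the open-ended data separately for all participants.

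The cost is one short form at visits that already take place, with no change to treatment, sample size or primary outcomes. There are two downsides:

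- **Smaller N for the checklist comparison.** Participants whose visits precede the change have open-ended data only. Recruitment began in March 2023 and the article appeared in November 2023, about 8 months later. At the planned 7 to 8 per month, 56 to 64 of 80 would have been enrolled by then. At the pace implied by the November 2024 end date (80 over about 20 months, or 4 per month), about 32 would have been. Later visits of those participants could still use the checklist.
- **Recall.** The first enquiry stays at 1 month, so specific prompting helps with effects that have already resolved but does not remove the delay.

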#### Auditing

Formal audits will be conducted at the request of DSMB or Institutional REB. Representatives from the Institutional Review Board/Independent Ethics Committee can examine trial records and personal health information to verify the accuracy of collected data. The sponsor has the responsibility to ensure that investigators and institutions involved in the trial allow monitoring, audits, Institutional Review Board/Independent Ethics Committee (IEC) reviews, and regulatory inspections. This includes providing direct access to source data/documents for these purposes.

### Ethics and dissemination

#### Research ethics approval

The EndPaRL study will be conducted in accordance with the ethical principles laid down in the Declaration of Helsinki, the protocol, Good Clinical Practice guidelines, and applicable regulatory requirements. Full written informed consent will be obtained prior to conducting any study activities. The study was reviewed and approved by the Research Ethics Board (REB). This trial has been registered on ClinicalTrials.gov website (NCT05818774), and results will be reported as per the Consolidated Standards of Reporting Trials (CONSORT) guidelines. Protocol modifications will be avoided but, if necessary, will be communicated to all relevant stakeholders including Institutional REB committees, participants, trial registry, and regulators.

### Criteria for subject withdrawal

Subjects have the right to withdraw from the study at any time, without providing a reason. In the event that a subject decides to prematurely discontinue the study, he/she will be asked if he/she can still be contacted for further information. This will be documented accordingly. If the subject has already received the study drug prior to withdrawal, the subject will be requested to be contacted for a safety follow-up visit.

When applicable, subjects should be informed of circumstances under which their participation may be terminated by the Investigator without their consent. The Investigator may withdraw subjects from the study in the event of intercurrent illness, adverse events, lack of compliance with the study or study procedures, any other reasons where the Investigator feels it is in the best interest of the subject, or at the request of the Research Ethics Board (REB). The reasons for withdrawal by the Investigator will be documented and explained to the subject. Should a subject decide to withdraw, all efforts should be made to complete and report the observations, particularly the follow-up questionnaires (if agreed to by the subject), as thoroughly as possible. If the reason for the removal of a subject from the study is an adverse event, the principal specific event will be recorded in the case report form. The subject will be followed until the adverse event is resolved if agreed by the subject.

### Ancillary and post-trial care

No additional provisions will be made for post-trial care, and routine clinical care will be provided by the participant’s primary physician. If patient harmed as a direct result of taking part in this study, all necessary medical treatment will be made available to no cost for patient.

### Dissemination policy

Study results will first be disseminated at local, national, and international conferences and submitted for publication in a peer-reviewed journal. Authorship on the manuscript submitted for publication will be based on the contributions of the authors to the study.

### Additional studies

If the EndPaRL study achieves non-inferiority for end-on radiofrequency lesioning, we plan to perform a cost-effectiveness study to compare the two techniques for RFN of the CMBN in patients presenting with chronic, moderate-to-severe neck pain in the context of cervical zygapophyseal joint osteoarthritis.

## Discussion

Pain in the neck has a high prevalence and the cervical facet joints affected by trauma or degeneration are often generators of this pain. There are limited effective options for treating this pain with only RFN showing evidence of effectively reducing pain from cervical facet joint dysfunction [9]. The purpose of RFN is to ablate the CMBN using high temperatures and provide longer pain relief than simple nerve or intra-articular blocks. The procedure involves first positioning a needle electrode over the nerve at its corresponding bony anatomy. The conventional technique for performing RFN of the CMBN involves introduction and advancement of the RF cannula from a posterior to anterior direction that is parallel to the cervical facets and the CMBN that run on these facets. The efficacy of this approach has been demonstrated in several studies [2–5]. More recently, an end-on technique has been proposed that involves introduction and advancement of the RF cannula from a lateral to medial direction that is perpendicular (end-on) to the cervical facets and the CMBN, thereby reducing the cannula path length and discomfort for the patient. However, the efficacy, benefits, and adverse effects of this end-on approach have not been compared to the conventional parallel approach.

This non-inferiority study aims to compare the efficacy and effectiveness of the conventional parallel approach versus the end-on approach for RFN of the CMBN in patients with cervical facet joint syndrome. Eighty participants will be included and will be divided between the two groups. Participants and assessors will be blinded to the treatment allocation. Data on will be collected from baseline up to 12 months after the RF procedure on the analgesic benefit, neck-related disability, physical activity, sleep, participants’ impression of change, procedural complications, adverse effects, and analgesic requirements. The methodology will involve the use of wearable technology to assess physical activity and sleep, validated questionnaires for all the outcome domains, and it will be the first to compare the two techniques of RFN of the cMBN.

This trial will help to identify if the end-on approach for RFN of the CMBN is an effective and safe alternative to the conventional parallel technique for relieving neck pain originating from the cervical facet joints. The investigators hope the knowledge from this trial will be widely implemented to improve patients’ health and quality of life.

